### Plans to promote participant retention and complete follow-up {18b}

A range of retention strategies will be used, based on a systematic review of the evidence of methods to increase response rates [65] and designed in collaboration with our study PPI group. The retention strategies include:Collection of data enabling multiple methods of contacting participants (phone, email, post)Pre-notification of questionnaires using priming calls and SMS messagingTwo reminders approximately 2 to 3 weeks later to non-responders, the first including the full questionnaire and the second a much shorter questionnaire collecting data only on the primary outcome and the EQ-5D-5LThank you card and£10 gift voucher to thank participants for their time completing questionnaires

### Data management {19}

Data collection forms transferred to/from the CTRU will be coded with a trial number and will include two participant identifiers, the participant’s initials and date of birth. Study data will be held securely on paper and electronically at the University of Leeds CTRU, and appropriate processes put in place for the transfer, storage, restricted access, and disposal of personal information. Relevant Standard Operating Procedures, Guidelines and Work Instructions in relation to data management, processing and analysis of data will be followed. Following the end of the trial, data will be archived for a minimum of 7 years.

### Confidentiality {27}

All information collected during the course of the trial will be kept strictly confidential. Information will be held securely on paper and electronically; paper copies in locked file cabinets and electronic copies in password-protected files or databases secured with password-protected access systems. All records that contain personal identifiers, such as informed consent and contact details forms, will be stored separately from study records identified by Trial ID code.

Once the study is completed, sites will archive all study data until authorisation for confidential destruction is provided by the study sponsor. Electronic data transferred between sites, the CTRU or the University of Nottingham will be encrypted. Data will be archived at secure facilities at the University of Nottingham and University of Leeds.

### Plans for collection, laboratory evaluation and storage of biological specimens for genetic or molecular analysis in this trial/future use {33}

Not applicable, no specimens collected.

## Statistical methods

### Statistical methods for primary and secondary outcomes {20a}

A detailed statistical analysis plan will be finalised and agreed by the research team prior to analysis.

A single final analysis is planned after the trial is closed to recruitment and follow-up and when the full database has been cleaned and locked. Analyses will be completed by the CTRU statisticians using SAS version 9.4 [66].

The primary analysis will compare the proportions of participants in work/education for ≥ 80% of the their pre-injury hours 12 months post-randomisation between arms, using a two-level mixed effects logistic regression model, accounting for therapist-level clustering (in both arms) as random effects. The model will adjust for treatment allocation, data informing stratification factors (site, age, sex, time since injury and ISS; included as continuous covariates where applicable) and other relevant known predictors of the outcome as fixed effects. If a participant is unable to report their working status, e.g. if they are dead, this will be taken as they have not returned to work. Otherwise missing data will be assumed missing at random and multiple imputation will be used in primary analyses.

Analysis of secondary outcomes at 3, 6 and 12 months will use the same approach as the analysis for the primary outcome measure with the relevant model for the type of outcome variable using multi-level linear (adjusted for baseline where appropriate), logistic or Cox regression as appropriate.

Results will be expressed as point estimates (mean difference, odds ratios, hazard ratios), together with standard errors, 95% confidence intervals and *p* values. Unadjusted and adjusted ICCs will also be reported.

### Interim analysis {21b}

No formal interim analyses are planned. An internal pilot analysis focussed on recruitment figures will be performed 10 months after the first two sites have opened (for recruitment rates) and 12 months later (for retention rates), participants from this analysis will be included in the main trial*.*

### Methods for additional analyses {20b}

Descriptive data (e.g. total numbers of screened patients, patients eligible for participation, those providing consent, reasons for non-entry) will be reported and baseline characteristics for each study arm summarised. Baseline characteristics of those lost to follow-up will also be compared with those not lost to follow-up to assess for bias at each follow-up timepoint. Quantitative summaries of intervention delivery will evaluate uptake of the ROWTATE VR intervention, adherence to the processes and quality of intervention delivery. Data on usual care and adverse events will be summarised descriptively.

An exploratory Complier Average Causal Effect (CACE) analysis will be conducted on the primary endpoint in order to measure the impact of the intervention amongst participants who complied with the intervention (attendance at ≥ 70% sessions). The CACE models will use the same multi-level mixed effects modelling techniques as the primary analysis model to ensure reasonable comparisons can be made. Sensitivity analysis will be conducted to vary the definition of compliance (i.e. attendance at > 60%, > 80% sessions).

For the primary outcome, potential moderators (via an interaction between the treatment arm and potential moderator) of the treatment effect will be explored for key baseline factors (i.e. age, gender, job category, anxiety, depression, type of injury and injury severity) and mediators of the treatment effect will be explored for post-randomisation factors (i.e. number and proportion of intervention sessions attended, work/education intentions, job/education retention, sickness absence, work/education at 3/6 months, anxiety, depression, benefits claimed, financial stress and pain).

### Analysis population definitions and methods for handling missing data {20c}

Analyses will be conducted on the intention to treat (ITT) population, which includes all randomised participants, regardless of adherence to the intervention, analysed as randomised.

Missing data are expected at the item, outcome and time point levels. Where questionnaires have published scoring protocols, detailing the handling of missing item data, these will be followed. If not, missing items will be imputed as the mean of non-missing data for that item where 50% or more items for a scale are available. Mechanisms for missing outcome data will be explored and missing data will be imputed via multiple imputation. Sensitivity analysis will explore the impact of employing different missing data handling strategies, including analysis to the availability of data.

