### Sample size {14}

The planned sample size for the study is 722 recruited participants equally distributed across usual care and ROWTATE VR intervention plus usual care. This will provide at least 90% power, at the 5% significance level, to detect a between-group 15% absolute difference in return to work rates, with an expected 60% return to work rate in the control arm, allowing for up to 30% loss to follow-up at 12 months and design effect up to 1.221. The design effect appropriately inflates the required sample size for a individually randomised controlled trial to account for clustering resulting from therapist-delivered interventions in both study arms. The design effect assumes an intra-cluster coefficient (ICC) less than or equal to 0.03 (80, 81); an expected cluster size (number of participants seen per therapist) of ~ 11 participants (~ 8 analysable participants) with four therapists per site in the intervention arm across eight sites, and a coefficient of variation in cluster size less than or equal to 0.25 (i.e. cluster sizes ranging 3–14 participants). The remaining therapists across the eight sites will provide usual care.

This sample size is sufficient with 93% power to detect a moderate 0.3 effect size between randomised groups in health-related quality of life measured by the EQ5D using the same assumptions as the primary outcome calculation. This is based on a standard deviation (SD) of 0.248 in those who had not returned to work and 0.176 in those who had returned to work obtained from unpublished data from our Impact of Injuries Study [55]. The minimal important difference for the EQ-5D has been estimated to be 0.074 [56].

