Secondary and health economic outcomes will be measured by a combination of bespoke questions and standardised tools. Bespoke questions will assess work/education intentions, time to return to work/education, retirement, sickness absence; and health and social care resource use. Outcomes measured using standardised tools include:Health-Related Quality of Life using with the EuroQol EQ-5D-5L which measures self-reported health outcomes regarding mobility, self-care, usual activities, pain/discomfort and anxiety/depression [54]. It has been recommended by guidelines for use in comprehensive injury populations including injury of moderate severity and major trauma [57]Psychological wellbeing using:PHQ-9 which is designed to screen for depression [38] in a variety of medical settings and is highly sensitive and specific [58]. It has been found to be a valid tool amongst acutely injured trauma survivors [59] and have high sensitivity, specificity and test–retest reliability in people with traumatic brain injury [60].GAD-7 which is used to screen for generalised anxiety disorders in a range of medical settings [39] and is highly sensitive and specific [61] and shows high internal consistency amongst people with TBI [62].IES-6 to measure post-traumatic distress symptoms. It has been shown to have high internal consistency, and high sensitivity and specificity with a cut-off of a mean score of 1.75 for a diagnoses of PTSD based on the Clinician Administered PTSD Scale [50]. It has also been shown to predict psychological distress in burn survivors at 6 months and 2 years post -injury [63].Work self-efficacy using Work Ability Index which measures participants’ self-reported estimation of ability to do their work with respect to work demands, health and mental resources [51]. Items 1 (workability scale) and 2 (separate questions on physical and mental demands) will be used. Item 1 has been shown to predict sustainable RTW in construction workers with musculoskeletal conditions [64].Financial impact of injury using Financial Chronic Stress Scale (3 item scale) which measures satisfaction with financial situation, difficulty meeting monthly bill payments and monthly finances [52].Purpose in Life Test – Short Form which assesses a person’s perceived meaning and purpose in life. The scale contains 4 items measuring presence of goals, goal completion and meaning in life. Responses are on a Likert scale ranging from 1–7 with a total score ranging from 4 to 28. Higher scores on this scale are indicative of greater reported purpose in life. It has been shown to have acceptable reliability [53].

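### For scales without a published missing-item rule, the protocol as worded fills a missing item from other participants' answers, not the participant's own; one sentence needs correcting

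*Protocol article*

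**What the plan says.** All of this is in the protocol article, under the analysis populations and missing data heading {20c}. The section expects gaps at several levels: "Missing data are expected at the item, outcome and time point levels". For single items it sets an order of precedence. First, "Where questionnaires have published scoring protocols, detailing the handling of missing item data, these will be followed". Failing that, "missing items will be imputed as the mean of non-missing data for that item where 50% or more items for a scale are available".

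Whole missing outcomes are dealt with in a separate sentence: "Mechanisms for missing outcome data will be explored and missing data will be imputed via multiple imputation". A general sensitivity analysis follows: "Sensitivity analysis will explore the impact of employing different missing data handling strategies, including analysis to the availability of data".

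The section does not say which scales fall under the fallback rule. Nor does it say whether the item mean is taken over both arms or within arm. The Assessment instruments section describes two short scales that show how much one blank can weigh: the 3-item Financial Chronic Stress Scale and the Purpose in Life Test – Short Form, of which it says "The scale contains 4 items measuring presence of goals, goal completion and meaning in life".

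**The concern.** The rule and its condition do not fit together. A mean taken for an item is a mean down a column of the data set, over participants. Requiring that half of the scale's items be answered makes sense when the fill-in is a mean along the row, from the participant's own answers: there must be enough of them to represent that person. A column mean needs no such condition.

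If the sentence is programmed as written, a participant with severe scores on the answered items receives the average participant's answers on the rest, which pulls the score towards the overall mean. On a short scale the pull is strong, because the 50% condition allows 2 of 4 items or 1 of 3 to be filled this way. What is at stake is the estimated arm difference, or its precision, on those secondary scales. Financial stress is also listed among the exploratory mediators of the treatment effect.

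**Working it through.** **What the sentence can mean.** A participant who left an item blank has no value of it at that time point, so the non-missing data for the item must come from other people. Borrowing the same person's answer from another visit is not mentioned, and could not work for the Purpose in Life scale, which is collected only at 12 months. No other section changes the wording.

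**The plan's own figure, as a check.** The point does not depend on the sample size, but it reproduces closely. For 60% v 75%, two-sided 5% and 90% power, n per arm = (1.96·√(2·0.675·0.325) + 1.2816·√(0.6·0.4 + 0.75·0.25))² / 0.15² = 203 after rounding up. Then 203 × 2 × 1.221 / 0.70 = 708, against the planned 722 (within 3%); power at 722 is 90.6%. None of these inputs involves a multi-item scale.

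**Item means pooled over arms.** Let each of k items carry an arm difference δ, so a complete sum score carries kδ. Suppose a share f of each arm misses q items and both arms receive the same fill-in. Those participants contribute (k − q)δ. The average is

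(1 − f)·kδ + f·(k − q)δ = kδ·(1 − f·q/k).

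The expected difference is therefore multiplied by 1 − f·q/k.

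**Simulation.** Settings: 253 per arm (722 × 0.70 / 2 = 252.7), true effect 0.30 SD, inter-item correlation 0.5, 1,500 runs, no therapist clustering. The 0.30 SD is borrowed from the article's EQ-5D power statement for illustration. The correlation, f and q are assumptions. Effects are in SD units of the complete score.

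| k | q | f | 1 − f·q/k | Complete data | Pooled item mean | Own-scale mean | Power %: complete / pooled / own |
|---|---|---|---|---|---|---|---|
| 4 | 1 | 5% | 0.9875 | 0.302 | 0.298 | 0.302 | 92.7 / 92.3 / 92.4 |
| 4 | 1 | 10% | 0.975 | 0.297 | 0.289 | 0.297 | 91.8 / 91.5 / 91.9 |
| 4 | 1 | 20% | 0.95 | 0.303 | 0.287 | 0.303 | 92.1 / 91.6 / 91.9 |
| 3 | 1 | 20% | 0.933 | 0.297 | 0.277 | 0.297 | 90.3 / 89.8 / 89.7 |
| 4 | 2 | 20% | 0.90 | 0.299 | 0.269 | 0.298 | 91.3 / 89.7 / 90.5 |
| 4 | 2 | 40% | 0.80 | 0.296 | 0.236 | 0.296 | 90.6 / 87.7 / 88.9 |

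The simulated ratios follow the formula; for example, 0.269 / 0.299 = 0.90. The own-scale mean stays within 0.001 of the complete-data estimate.

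**Why power hardly moves.** The pooled fill-in also narrows the score distribution. With 2 of 4 items missing in 20% of participants the SD falls from 1.010 to 0.936. The standardised effect goes from 0.299 / 1.010 = 0.296 to 0.269 / 0.936 = 0.287, a loss of about 3%, while the raw difference loses 10%.

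**Item means taken within arm.** In the same setting the difference is kept (0.299), but the SD is 0.938 instead of 1.010, about 7% too small, and the rejection rate rises to 93.4% against 91.3% with complete data. The estimate is right and its precision is overstated.

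**The case against.** Several objections carry weight.

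- **It may be a slip.** The 50% condition suggests that the authors meant the participant's own mean, and the article says a detailed analysis plan will follow. That favours a modest tone. But this is a rule stated explicitly, not a detail left for later, and anyone coding it literally would compute the item mean.
- **It is only a fallback.** A reader might infer that every questionnaire is affected, including the PHQ-9, GAD-7 and IES-6. The article does not support this: published scoring rules come first, and it does not say which instruments lack one. The 3- and 4-item scales illustrate length only.
- **Shrinkage is conditional.** A reader might infer that treatment differences must be attenuated. That holds only if means are pooled over arms, which the text does not state.
- **Larger percentages mislead.** Among participants with missing items alone the factor is 1 − q/k, or 0.50 to 0.75 on a 4-item scale. No analysis is planned in that subgroup, so those figures do not describe any trial result.
- **Ignored uncertainty does not separate the rules.** The own-scale mean is also a single fill-in treated as observed.
- **The simulation suits the remedy.** It uses exchangeable items. Where items differ in level or content, as they may on the Financial Chronic Stress Scale, the own-scale mean need not be exactly unbiased.

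The planned sensitivity analysis could cover item handling but does not name it. These points limit the size and certainty of the concern. They do not remove the mismatch in the sentence.

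**Conclusion.** The concern holds in a limited form. For multi-item secondary scales without a published missing-item rule, the sentence as written imputes from other participants, under a condition that belongs to imputing from the participant's own answers.

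If means are pooled over arms, the expected difference on a 4-item scale shrinks by 1.25–2.5% with 1 item missing in 5–10% of participants, and by 5–10% with 1–2 items missing in 20%. The 20% shrinkage at 2 of 4 items missing in 40% is an extreme. If means are taken within arm, there is no shrinkage but variance is understated. All missing-item rates are assumed, because the article gives none, and equal missingness in the two arms is assumed too.

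Power is not the argument. It falls by 0.3 to 1.6 points for up to 20% of participants with partly missing scales, and the own-scale mean does not always recover it. The gain from correcting the sentence is an estimate that is not pulled towards the overall mean. The primary return-to-work outcome, built from work-status and hours questions, and the sample size of 722 are unaffected. It should be corrected before analysis, as a minor change.

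**What to change.** Reword the fallback rule in the protocol and carry it into the analysis plan. For example: *a missing item is replaced by the mean of the participant's own answered items on that scale at that time point, provided at least 50% of the items are answered; items with different response ranges are rescaled first; otherwise the scale score is treated as missing and left to multiple imputation.* Imputing at item level within the multiple imputation is an acceptable alternative, and it carries the uncertainty that a single fill-in does not.

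The cost is one sentence, with no new data and no change to the sample size. The downside is that the own-scale mean is still a single fill-in and assumes reasonably similar items within a scale. It also widened the score SD slightly in the simulation (1.037 against 1.010 with 2 of 4 items missing in 20% of participants). Where a scale's items are clearly unlike each other, item-level multiple imputation is the safer choice.

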### Plans to give access to the full protocol, participant-level data and statistical code {31c}

Data will be available upon request and subject to approval by the study funder, sponsor and TSC. A data sharing agreement will be required prior to access /sharing of any study data.

#### Health economic analysis

An economic evaluation alongside the trial will be conducted to determine whether the ROWTATE VR intervention plus usual care is cost effective compared to usual care alone at 12 months post-randomisation. As recommended by NICE guidance [67] (2022), the primary health economic analysis will take a NHS and personal social services cost perspective. Secondary analysis will use a societal perspective to capture the broader effects of return to work (RTW) on out-of-pocket expenses and economic effects on the individual, carers and families notably the productivity gain from RTW and a reduction in time spent on caring for the patient. This will enable a broader societal perspective to be reported alongside a health service perspective.

A detailed micro-costing within the trial for both intervention and usual care arms will be conducted, using a patient resource proforma designed for the trial. The proforma has been designed based on a patient focus group which identified key cost drivers for trauma. It will collect patient-level resource information on all aspects of initial and follow-up resources used by the patient, NHS and community care services (Table 3) at 3, 6 and 12 months on follow-up questionnaires from all participants in both arms. A monthly calendar will be provided for participants to record daily resource use to facilitate questionnaire completion. Intervention-specific resource use will be derived from intervention CRFs (Table 3).

Resource use units from patient follow-up questionnaires and therapist CRFs will be transformed to costs applied, using national sources such as NHS and community services prices, such as the Unit Cost of Health and Social Care, Personal Social Services Research Unit (PSSRU), the British National Formulary (BNF) and the National Reference Cost Collection.

The main outcome measure will be the QALYs derived from the EQ-5D-5L questionnaire completed at baseline, 3, 6 and 12 months. These will be combined with patient and therapist reported health care and societal costs to inform the cost-utility analysis from an NHS perspective and a separate secondary analysis taking a societal perspective. No discounting will be applied to derived QALYs or costs due to their being incurred within a 12-month period. Patient responses to the EQ-5D-5L will be converted into utility scores using standard UK population tariff values. These will be transformed into QALYs using the trapezium rule to calculate the area under the curve. The value set for EQ-5D-5L has not yet been published by NICE (see 2019 official statement) [68]. Whilst there is currently controversy around the EQ-5D-5L tariff, we will map the EQ-5D-5L values back to the EQ-3D using the Crosswalk Index Value Calculator to provide consistency with current NICE requirements [69].

The economic outcomes of the cost-utility analysis are an Incremental Cost-Effectiveness Ratio (ICER), along with the incremental monetary benefit, both of which represent the monetary value to the NHS when the willingness-to-pay threshold for a specified outcome is known. Specifically, we will use the net monetary benefit framework to estimate the extent to which the intervention is a cost-effective option compared to usual care at the NICE threshold of £20,000–£30,000 per QALY gain. If the incremental net benefit is positive, then the intervention is cost effective at the desired threshold. Cost-Effectiveness Acceptability Curves (CEACs) will be constructed to show the probability that the ROWTATE VR intervention is cost effective compared to usual care across a range of willingness-to-pay thresholds. Key cost drivers will be examined using sensitivity analysis.

